#### Enhanced Usual Care

The EUC intervention will include basic psychoeducation regarding depression and anxiety, as well as resources on available evidence-based care available in Jordan. This will be delivered through a website where participants register to gain access. The information provided to those in EUC will also be provided during the psychoeducation session to those enrolled in the STARS intervention. Available resources will include a list of organizations that offer evidence-based mental health and psychosocial support in Jordan—as this study is taking place at a national level, a list has been created of the resources available across the country so that those in need can access services close to their physical location.

### Measures

All assessments will take place remotely and be hosted through Qualtrics, a secure data collection online platform.

#### Screening Measures

The screening assessment consists of the K10 to assess levels of psychological distress [38] and screening questions to determine the imminent risk of suicide informed by the WHO mhGAP Intervention Guide 2.0 [47]. The K10 assesses general psychological distress and consists of 10 items corresponding to symptoms of depression and anxiety experienced in the preceding 30 days. Items are rated on a 5-point Likert scale ranging from 1=none of the time to 5=all of the time, with scores determined through the sum of the items (range 10-50). Higher scores are indicative of higher levels of distress; a cutoff score of 20 will be used to determine inclusion as it has been previously shown to indicate moderate to significant levels of distress [48]. The K10 will also be used as a secondary outcome measure. The imminent risk of suicide, as defined by the WHO Mental Health GAP program, will be screened through 3 questions [47]. Participants will be asked to indicate whether they have had thoughts of suicide in the preceding 30 days and if a positive response is recorded, follow-up questions regarding prior attempts or future plans will be asked. Participants who indicate imminent risk as determined by the follow-up questions will be excluded from the study and provided with on-screen information directing them to support services.

#### Primary Outcome

The primary outcome will be levels of depression and anxiety as determined through the HSCL-25 [39]. The HSCL-25 is a 25-item questionnaire consisting of 2 subscales assessing symptoms of depression and anxiety; 15 items correspond to symptoms of depression and 10 correspond to symptoms of anxiety. The validity and psychometric properties of the questionnaire have been well established in both adults and youths or adolescents [49,50]. Additionally, an Arabic version of the HSCL-25 has been previously validated [51] and has been used successfully among adults in Jordan during a previous study determining the effectiveness of a scalable psychological intervention [52].

#### Secondary Outcomes

The WHODAS 2.0 will be used to assess levels of impaired functioning [40]. The measure assesses general disability people experience in their daily lives over the prior 30 days across 6 domains: self-care, getting along with others, cognition, mobility, participation, and life activities. The 12-item version will be used, which includes 2 contributing items from each domain. Difficulties are scored on a 5-point scale ranging from 0=none to 4=extreme, with total scores ranging from 0 to 48. The measure has been widely validated globally, with specific psychometric studies taking place in youth populations [53] and on the Arabic version [40,54]*.*

The PSYCHLOPS measure will be used to understand participants’ primary problems and how they impact daily functioning, and to track improvements of these problems over the course of the study [42]. The measure includes 4 items spanning 3 domains: problems, functioning, and well-being. Free-text responses are provided for the problem and functioning domains, with impacts on daily life being scored on a 6-point ordinal scale. Posttreatment and follow-up versions of the measure include an overall valuation question to determine the improvement of these problems. The PSYCHLOPS has been validated in a number of contexts [55,56].

Psychological well-being and quality of life will be assessed through the WHO-5 [41]. The WHO-5 measures subjective positive well-being across 5 items scored on a 6-point Likert scale, with responses ranging from 0=at no time to 5=all of the time. Total scores range from 0 to 25, with higher scores indicating higher levels of well-being. The WHO-5 has been used globally in research and across a number of clinical settings [41] and has previously been validated in an Arabic sample [57].

The SHS-A will be used to assess perceived agency [43]. The agency subscale consists of 3 items observing perceived levels of goal-directed energy measured on an 8-point Likert scale ranging from 1=definitely false to 8=definitely true. The potential mediation effect of agency on treatment outcomes will be explored in the secondary analysis.

#### Other Measures

To capture any mental health services that participants received prior to or during the study period, 2 items will be included in postassessments to capture information on the use of psychological or counseling services and medications (each item answered with yes or no).

Those randomized into the STARS intervention will complete the Patient Health Questionnaire, 2-item version (PHQ-2) [58] during every other session. The PHQ-2 has been shown to allow for the detection and monitoring of depression over time and will allow the research team to identify potential worsening of symptoms in participants during the intervention phase [58]. The measure inquiries about symptoms of depression over the past 2 weeks, with items scored on a 4-point Likert scale ranging from 0=not at all to 3=nearly every day, with scores ranging from 0 to 6.

Finally, user satisfaction of the STARS intervention will be assessed through a version of the Client Satisfaction Questionnaire, a scale intended to measure client satisfaction with health services, adapted specifically for web-based health interventions [44]. The questionnaire includes 8 items scored on a 4-point Likert scale ranging from 1=does not apply to me to 4=does totally apply to me. The assessment will be offered to participants during the post-intervention assessment as an optional additional questionnaire.

### Sample Size

A total of 344 participants will be included in the RCT. This sample size calculation was based on the results of prior trials exploring the effectiveness of comparable digital interventions which report effect sizes (Cohen *d*) ranging from 0.48 to 0.56 [17,18,59]. In addition, a similar effect size was used to determine the sample size for a similar RCT observing the effectiveness of a WHO-developed digital health intervention, based on a conservative, yet clinically significant effect size of 0.5 [60]. Assuming an effect size of 0.5 at a 3-month follow-up (power=90%; α=0.05, 2-sided), the trial would require 172 participants (STARS=86 and EUC=86). Given the high attrition rates reported in digital intervention studies, a conservative attrition rate of 50% was assumed. This attrition rate was informed by the results of the feasibility RCT and comparisons with protocols for similarly designed studies.

### Statistical Analysis

To measure baseline differences between the 2 treatment arms, 2-tailed *t* tests will be conducted for continuous variables and chi-square tests for categorical data. To determine the effectiveness of the STARS intervention, intention-to-treat analysis will be conducted to compare the mean difference between STARS and EUC at baseline, post intervention, and 3-month follow-up. Differential change over time between treatment arms will be assessed using linear mixed models that accommodate missing data at subsequent assessments and provide differential slopes of trajectories between conditions. Hierarchical linear models study treatment effects because this allows the number of observations to vary between participants and handles missing data by using maximum likelihood estimation methods. Missing data will be assumed to be random if participants retained and not retained at 3 months do not differ on baseline characteristics. Fixed (intervention and time of assessment) effects and their interactions will be entered in unstructured models to yield indices of the relative effects of the treatments; time of assessment included baseline, post treatment, and 3-month follow-up. Analyses will focus on the primary outcome and secondary measures, with the main outcome time point being the 3-month follow-up relative to baseline. A subsequent per protocol completers analysis will be conducted, only including those who completed the 3-month follow-up, in order to assess the robustness of the primary analysis.

In addition to these analyses, the role of potential moderators and mediators, such as agency, on outcomes will be explored independently using the PROCESS macro. Two-tailed tests with a significance level of *P*<.05 will be reported for all analyses.

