### Randomization and Blinding

Participants will be randomized to receive either STARS or EUC at a 1:1 allocation ratio following the baseline assessment. The randomization sequence will be developed through Qualtrics software and will be automated and embedded in the baseline questionnaire, with participants having their group allocation conveyed to them immediately upon completion of the assessment. Given the high proportion of Syrian refugees and other populations residing in Jordan, randomization will be stratified on a 1:1 ratio (Jordanian or Palestinian vs Syrian or other nationalities). Given that questionnaires are self-administered online, the outcome assessments will not be blinded.

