### Data Management, Trial Monitoring, and AE Reporting

All assessment data will be collected electronically in Qualtrics. Participants will receive personalized Qualtrics links for their baseline, post-, and 3-month follow-up assessments so that assessments can be linked to each other. Only the research team will have access to the data in Qualtrics. Deidentified data stored from the STARS intervention (eg, PHQ-2 scores, free-text responses, session completion date) are available to e-helpers and the research team through the OpenDialog website. Data collected online will be held securely and separately from study data, according to the relevant data protection laws. Data will be deidentified and stored confidentially at the University of New South Wales after transferring to an SPSS database.

An identifying key list (a list connecting names to numbers) will be kept by the project manager at IFH. All downloaded electronic data will be pseudonymized and stored on password-protected computers. Hardcopy files of the study, such as supervision notes, will be stored in locked cabinets at IFH. No identifiable data will be used in publications or presentations. Trial monitoring will be done by WHO staff on a biweekly basis to ensure the accuracy of data storage and output.

AEs or serious AEs (SAEs) refer to any undesirable experience of a participant during the trial, whether or not considered related to the trial procedures or to the STARS or EUC interventions. All AEs or SAEs reported spontaneously by participants or observed by the research team or e-helpers will be reported to the IFH clinical supervisor for immediate action and resolution where required. All SAEs will be reported to the local ERC within 24 hours of being informed about the event, and a summary of AEs will be reported to the local ERC every three months. The local ERC will review any SAEs as soon as possible and the summary of AEs during their regular meetings. They will determine any appropriate action with respect to ongoing study conduct. Additionally, all SAEs will be reported to the WHO ERC. As STARS is nonpharmacological and there exists a broad evidence base for the safe use of e-interventions and therefore a low risk for adverse effects, no Data Monitoring Safety Board will be installed for this study. Adverse events will be monitored and reported to the local ethics committee.

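### With 50% attrition planned, the baseline-only randomness rule and the completers check cannot detect dropout caused by stopping STARS, so the intention-to-treat effect could be misstated unnoticed

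*Protocol article*

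**What the plan says.** Under Sample Size, the protocol article states that "a conservative attrition rate of 50% was assumed".

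Under Statistical Analysis it commits to the following:

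- **Population:** "intention-to-treat analysis will be conducted to compare the mean difference between STARS and EUC".
- **Model:** "Differential change over time between treatment arms will be assessed using linear mixed models that accommodate missing data at subsequent assessments". The fixed effects named are arm, time of assessment and their interaction, fitted by maximum likelihood.
- **Rule on missingness:** data are taken to be missing at random when participants retained at 3 months and those lost show no baseline differences.
- **Robustness check:** a repeat analysis restricted to people who completed the 3-month assessment.

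Under Data Management, Trial Monitoring, and AE Reporting, the article says: "Deidentified data stored from the STARS intervention (eg, PHQ-2 scores, free-text responses, session completion date) are available to e-helpers and the research team". The Other Measures and Safety Considerations sections present the PHQ-2 as a way of monitoring participants during the intervention. Nothing in the article uses the STARS usage records in the missing-data rule, the model or a sensitivity analysis.

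**The concern.** STARS is a ten-lesson course with five support calls. The comparator is an information website, of which the article says "This will be delivered through a website where participants register to gain access". Only one arm therefore has a graded course that a person can abandon. Stopping happens after randomization, and it may be related both to whether the questionnaires are answered and to the 3-month score.

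A STARS participant who answers neither the 8-week (T2) nor the 3-month (T3) assessment contributes a baseline score only. The likelihood then implicitly gives that person the course of STARS participants with the same baseline who did respond. If the responders are mostly people who kept going, and if they do better, the effect among all randomized is overstated.

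None of the planned safeguards would show this. The model has no term for engagement, the rule looks only at baseline, and the completers analysis is made in the same selected group, so its agreement with the primary result would be no reassurance. The Conclusions section links open-access release to the result of this trial and a second one.

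**Working it through.** **Plan's own figure.** "power=90%; α=0.05, 2-sided), the trial would require 172 participants (STARS=86 and EUC=86". With d = 0.5, the normal approximation is 2 x (1.960 + 1.282)^2 / 0.5^2 = 84.1, so 85 per arm. The two-sample t-test gives 85.03, so 86 per arm and 172 in total. Then 172 / (1 - 0.5) = 344. The sample size is reproduced and is not in question.

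**Bias, closed form (T3 only).** Let p be the share of the STARS arm who stay in the course, dp and dq the benefit of stayers and quitters in SD units, rp the T3 response of stayers, and r = 0.5 the overall response. With EUC lost at random,

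bias = (dp - dq) x p x (rp / r - 1).

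Only r comes from the article; p, dp, dq and rp are assumptions. With p = 0.5:

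- Headline case (0.8 vs 0.2; response 75% vs 25%): 0.6 x 0.5 x (0.75/0.5 - 1) = 0.15, so 0.65 against a true 0.50.
- Mild case (0.6 vs 0.4; 65% vs 35%): 0.2 x 0.5 x (0.65/0.5 - 1) = 0.03.
- Reversed case (0.3 vs 0.7; 65% vs 35%): -0.4 x 0.5 x 0.3 = -0.06.

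**Bias, allowing for T2 scores.** Two sets of large-sample simulations (400,000 per arm) applied the likelihood analysis to data with some T2 scores. Set A has correlations of 0.5 between baseline and each later visit and 0.7 between T2 and T3; T2 is seen for all T3 responders and for 0%, 30% or 50% of the rest. Set B has a correlation of 0.6 throughout and monotone dropout.

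| Set | Benefit, stay / quit | T3 response, stay / quit | True | Planned model | With lesson completion |
|---|---|---|---|---|---|
| A | 0.8 / 0.2 | 75% / 25% | 0.50 | 0.65, 0.61, 0.58 | 0.50, 0.50, 0.49 |
| A | 0.6 / 0.4 | 65% / 35% | 0.50 | 0.52 to 0.53 | 0.50 |
| A | 0.6 / 0 | 75% / 25% | 0.30 | 0.39 to 0.46 | 0.30 |
| B | 0.7 / 0.3 | 65% / 35% | 0.50 | 0.56 | 0.50 |
| B | 0.7 / 0 | 75% / 25% | 0.35 | 0.51 | 0.35 |
| B, T2 well kept (95% / 85%) | 0.7 / 0 | 75% / 25% | 0.35 | 0.46 | 0.35 |
| B | 0.5 / 0.5 | 75% / 25% | 0.50 | 0.50 | 0.50 |
| B | 0.7 / 0.3 | 50% / 50% | 0.50 | 0.50 | 0.50 |
| B | 0.3 / 0.7 | 65% / 35% | 0.50 | 0.45 | 0.50 |

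Where both links hold, the bias runs from 0.02 to 0.16 SD. It is zero when stopping is unrelated to response or to outcome, and about -0.05 when quitters do better. The operative link is with outcome, not strictly with benefit. In a further set B run there was no treatment effect, but stayers were 0.4 SD better whichever arm they were in, with 65% / 35% response in STARS. The planned model gave 0.06 against a true 0.00.

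**Scale.** With 86 responders per arm the standard error is sqrt(2/86) = 0.15. The headline bias is about one standard error and the mild one about a fifth. A shift of 0.06 SD with no true effect would raise the two-sided rejection rate from 5% to about 6.8%.

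**Would the baseline rule notice?** With 0.7 / 0 benefit, 75% / 25% response and stopping unrelated to baseline, a single baseline comparison at N = 344 found no difference in about 95.5% of 4,000 simulated trials. That is what a 5% test must do when baseline carries no information. The point is that passing the rule says nothing about a cause of dropout that arises later.

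**Precision of an engagement-based analysis, headline case.** The 86 STARS responders split into 64.5 stayers and 21.5 quitters, each group weighted by one half: 0.25/64.5 + 0.25/21.5 = 0.0155. Adding 1/86 = 0.0116 for EUC and taking the square root gives 0.165, against 0.15.

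**The case against.** The strongest reply has five parts.

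- **The SAP may deal with it.** The quoted sentence is correct as statistics, and auxiliary variables and sensitivity imputation are often left to a SAP, which is not shown here. That stands for the absence of such analyses. It does not cover the baseline rule, which the article itself fixes, or the choice of a completers analysis as the robustness check.
- **No bias is shown.** A reader might infer that the effect is biased towards STARS. The documents do not support this: they give no data linking stopping to non-response or to outcome. People may also stop because they have improved, and selective loss in EUC, which the calculations set to random, could offset the bias or add to it.
- **Quitting is not the same as going missing.** A reader might infer that everyone who quits is credited with full benefit. Those who still answer keep their real scores, and those with T2 only contribute T2. In the headline case the model gives 0.65, not the 0.80 that would apply if all had continued.
- **The PHQ-2 is not available for everyone.** It is taken inside every other lesson, so it is absent or out of date for early quitters. Lesson count, with zero included, is the dependable variable.
- **Recovery of the truth is built in.** Dropout was simulated to depend on engagement alone. In practice an imputation using lesson count still assumes randomness within engagement level, and about 22 quitters with T3 scores would inform about 64 without.

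The last four points stand. They limit the claim and shape the fix, but they do not rescue the baseline rule.

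**Conclusion.** The concern holds as a conditional one. The model, the baseline rule and the completers check that the article fixes cannot detect dropout that depends on stopping STARS, and 50% attrition leaves ample room for it. If people who stop both answer less often and do worse at 3 months, the effect is overstated by about 0.02 to 0.16 SD in the assumed scenarios. If either link is absent the bias is zero, and it is about -0.05 SD if they do better. These sizes rest on assumed engagement, response and benefit figures and on random loss in EUC; only the 50% comes from the article. The stronger statement, that the planned estimate is biased in favour of STARS, is not established. This is an inexpensive improvement to the plan and does not show that the primary analysis is invalid.

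**What to change.** 1. Delete the rule that similar baselines justify assuming randomness. Describe baseline comparisons of retained and lost participants as descriptive only.
2. Keep the mixed model as the primary analysis. Beside it, prespecify a sensitivity analysis of the same 3-month contrast by multiple imputation carried out separately by arm. In STARS, the imputation model contains baseline HSCL-25, any T2 score and the number of lessons completed (zero included), with the PHQ-2 only where it exists. In EUC it contains baseline and any T2 score; the article mentions registration on the website but describes no usage log.
3. Use engagement in the imputation step only, never as a covariate in the outcome model, because it follows randomization.
4. Add a delta-adjusted or reference-based version for STARS participants lost to follow-up, since the imputation still assumes randomness within engagement level.
5. Always report the mixed model and the sensitivity analyses together. Do not let the observed difference between them decide which is the headline.

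The cost is a paragraph in the plan and the linkage of OpenDialog records to Qualtrics records. The article mentions an identifying key list but does not describe this linkage. The interval is somewhat wider (standard error about 0.165 against 0.15 in the headline case), and EUC has fewer auxiliary data than STARS. No new participants or measurements are needed. The Results section says no analysis had been done when the article was written, so prespecification was still possible then.

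### The rule for accepting missing at random, no baseline difference between retained and lost participants, can neither establish nor refute that assumption

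*Protocol article*

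**What the plan says.** The primary analysis in the Statistical Analysis section is a linear mixed model that "handles missing data by using maximum likelihood estimation methods". Baseline is one of its response occasions: "time of assessment included baseline, post treatment, and 3-month follow-up". The section then sets a condition for the missing-data assumption: "Missing data will be assumed to be random if participants retained and not retained at 3 months do not differ on baseline characteristics". The robustness check it names is an analysis restricted to those who completed the 3-month follow-up.

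The Sample Size section shows how much rests on this assumption: "a conservative attrition rate of 50% was assumed", so that of 344 randomized participants 172 are planned to be evaluable at the primary time point. The Limitations section names high attrition as a concern.

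**The concern.** MAR means that, given the data observed, missingness does not depend on the values that were not observed. Whether retained and lost participants look alike at baseline does not answer that question, in either direction.

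- **A pass is uninformative.** Participants may leave because they did badly, or well, after baseline. If that tendency is unrelated to the baseline score, the two groups look alike at baseline while MAR is false.
- **A fail is not evidence against MAR.** If sicker participants leave more often and baseline severity is in the likelihood, MAR holds and the estimate is sound. The comparison is closer to a partial check of missing completely at random, which maximum likelihood does not need.

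At stake is how the 3-month result will be read. With up to half of the primary endpoint missing under the planning assumption, a non-significant baseline comparison could be reported as support for the assumption on which the estimate depends.

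**Working it through.** **The plan's own figure.** For d = 0.5, two-sided alpha 0.05 and power 90%, the t-based calculation gives 85.03, rounded up to 86 per arm (power 90.3%), or 172 evaluable. Then 172 / (1 − 0.50) = 344. The sample size reproduces, and nothing below changes it.

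**Inputs.** From the article: 344 randomized 1:1 (172 per arm), 50% planning attrition, design effect 0.5 SD, test level 0.05, three occasions. Assumed, not in the documents: correlation between occasions ρ = 0.3 to 0.7; logistic dropout with a slope g of 0.5 or 1 in log-odds per SD; in the simulations, 40% of those lost at 3 months still seen at week 8.

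**Harmful dropout that passes.** Let dropout depend on Z, the standardized part of the 3-month score not explained by baseline, with P(drop) = expit(gZ). Half are lost. Among those retained, the mean of Z is shifted by −k(g), where k(g) = −2·E[Z·expit(−gZ)]. Numerical integration gives k(0.5) = 0.236 and k(1) = 0.413. With baseline and 3-month data only, the bias favouring STARS is √(1 − ρ²) × (k for STARS − k for EUC). The values of √(1 − ρ²) are 0.954, 0.866 and 0.714 for ρ = 0.3, 0.5 and 0.7.

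| Outcome-related dropout | ρ = 0.3 | ρ = 0.5 | ρ = 0.7 |
|---|---|---|---|
| Same slope in both arms | 0 | 0 | 0 |
| Slope 1 in STARS, 0.5 in EUC | 0.17 | 0.15 | 0.13 |
| Slope 0.5 in STARS only | 0.23 | 0.20 | 0.17 |
| Slope 1 in STARS only | 0.39 | 0.36 | 0.29 |

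For example, slope 1 in STARS only at ρ = 0.5: 0.866 × 0.413 = 0.358 SD.

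A simulation of the three-occasion maximum-likelihood model (800 trials per setting), which also uses the week-8 data, gave:

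- same slope 1 in both arms: bias at most 0.004 SD;
- slope 0.5 in STARS only: 0.15 to 0.23 SD;
- slope 1 in STARS only: 0.27 to 0.38 SD.

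Since Z is independent of baseline, the baseline test rejects at its nominal 5% in every row. The simulated pass rate was 94 to 96%, whether the bias was zero or large.

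**Harmless dropout that fails.** Let dropout depend only on the baseline score. Retained and lost then differ at baseline by 2k(g), which is 0.47 SD at slope 0.5 and 0.83 SD at slope 1. The test passed in 0 to 1.4% of simulated trials, while the bias was at most 0.006 SD.

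**Several characteristics.** If dropout is purely random and m independent characteristics are each tested at 0.05, the chance that at least one differs is 1 − 0.95^m: 1 − 0.95^6 = 0.26 and 1 − 0.95^10 = 0.40.

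**Power of the comparison.** With 172 retained and 172 lost, power to detect a 0.2 SD baseline difference is 46%, so a pass does not show similarity at baseline either.

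**The case against.** The strongest reply is that the sentence does no work in the estimation. The mixed model is primary whatever the baseline comparison shows, and the biases above would affect any MAR analysis under those mechanisms, including one with better wording. That stands. A reader might infer that the rule biases the trial or selects its model; the text does not support this.

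The larger biases are also chosen cases. The article gives no evidence that outcome-related dropout differs between arms, and with the same mechanism in both arms the arm difference is essentially unbiased. That stands too, so the size must be given as a range that includes zero. The rule still passes equally often at both ends of that range.

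The article speaks of characteristics in the plural, so the stated comparison would flag a difference more often than a single test at 5%. This is correct. It reduces the false reassurance but adds false alarms, since the extra flags carry no information about MAR.

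Other inferences go beyond the text. A reader might conclude that the comparison pools the arms, that nothing would be done if the groups differed, or that no sensitivity analysis exists. The article is silent on the first two, and the details may stand in a full protocol or SAP not shown. Nor is 50% a forecast: the article calls it conservative. The point rests only on the rule that is stated.

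**Conclusion.** The concern holds as an error of inference in a stated rule. A baseline comparison is not a test of MAR: it passes about 95% of the time on a single score whether the bias is nil or close to 0.4 SD, and it fails 99 to 100% of the time when dropout depends only on the modelled baseline score and the estimate is sound. The bias sizes rest on assumed slopes and correlations; the failure of the rule to discriminate does not. The finding that baseline-driven dropout is harmless applies to variables in the model. A baseline variable outside it that predicts both dropout and outcome would need to be added.

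The completers analysis does not repair this. It generally needs a stronger missingness assumption than the mixed model, so agreement between the two would reassure without good reason. The consequence is misreading of the primary result, not a wrong primary estimate. It should be fixed, but it does not invalidate the design.

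**What to change.** - Delete the conditional sentence. State that the mixed model assumes MAR given the variables it contains, and that this is a working assumption the data cannot verify.
- Keep the comparison of retained with lost participants as a description, by arm.
- Name in advance the baseline auxiliaries already collected, for example K10, prior care use and nationality stratum, and enter them in the model or an imputation model regardless of P values.
- Judge robustness by a prespecified missing-not-at-random analysis, such as a delta-adjusted or tipping-point analysis by arm, in addition to the completers analysis. If the SAP already contains one, refer to it here.

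The cost is wording and a little more analysis work. No new data are needed, and the sample size stays at 344. The article reports that no data analysis had been done at the time of writing, so the change could be made before results are known if that still holds.

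### Randomization is stratified by nationality, but the fixed effects stated for the mixed model include no stratum term; the cost is a slightly conservative analysis

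*Protocol article*

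**What the plan says.** Under Randomization and Blinding, allocation is 1:1 and "randomization will be stratified on a 1:1 ratio (Jordanian or Palestinian vs Syrian or other nationalities". The reason given is a design reason: "Given the high proportion of Syrian refugees and other populations residing in Jordan".

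Under Statistical Analysis, "Differential change over time between treatment arms will be assessed using linear mixed models". The terms are then listed: "Fixed (intervention and time of assessment) effects and their interactions will be entered in unstructured models". The contrast of interest is fixed as well, "with the main outcome time point being the 3-month follow-up relative to baseline".

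No section enters nationality in the model or explains its omission. Moderators are mentioned only as a separate exploratory analysis, and nationality is not named there.

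**The concern.** When allocation is balanced within strata, differences between strata cannot contribute to the difference between arms. The treatment estimate is then more precise than it would be under simple randomization. A model without the stratum does not see this. It leaves the between-stratum variance in its error term and reports a standard error that is too large. The test rejects less often than its nominal level, and some of the precision bought by stratifying is not used.

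The article gives the model's fixed effects explicitly, and the list does not match the randomization. An analyst who followed the published text would fit a model without the stratum.

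**Working it through.** **Inputs from the article.** The stratum has two levels. The planned effect is d = 0.5, with 90% power and two-sided α = 0.05. The evaluable sample is 86 per arm, attrition is 50%, and 344 are randomized.

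**Input not in the article.** R² is the share of the variance of the baseline-to-3-month contrast that the stratum explains. I assume 1-5%. The relevant quantity is the variance of change, not of the 3-month score: a nationality difference that is constant over time largely cancels from a contrast taken relative to baseline.

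**Step 1: reproduce the sample size.** The normal approximation gives n per arm = 2(1.960 + 1.282)² / 0.5² = 84.06, rounded up to 85. The t-test solution is 85.03, rounded up to 86, which gives 172, and 172 / (1 − 0.5) = 344. Power at 86 per arm is 0.903. The stated figures reproduce, and the stratum has no part in them.

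**Step 2: upper bound, with exact balance within strata in the analysed sample.** Set the total variance to 1. The unadjusted model reports a variance proportional to 1, while the true variance is proportional to 1 − R².

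- Ratio of reported to true standard error = 1/√(1 − R²)
- True type I error = 2[1 − Φ(1.96/√(1 − R²))]

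| R² (assumed) | SE ratio | Type I error |
|---|---|---|
| 0.01 | 1.005 | 0.0489 |
| 0.02 | 1.010 | 0.0477 |
| 0.05 | 1.026 | 0.0443 |

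**Step 3: allow for 50% random attrition.** Balance at randomization does not survive dropout intact. If a random half is retained, about half of the stratum-imbalance variance that simple randomization would carry returns. The true variance is then about (1 − R²) + 0.5R² = 1 − R²/2, so R²/2 replaces R² in the formulas.

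| R² (assumed) | SE ratio | Type I error |
|---|---|---|
| 0.01 | 1/√0.995 = 1.0025 | 0.049 |
| 0.05 | 1/√0.975 = 1.013 | 0.047 |

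A simulation agrees. It balanced 344 participants at randomization, with 50% random dropout, an assumed 30% share for the smaller stratum, R² = 0.05 and 40,000 runs. Type I error was about 0.047.

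**Step 4: power.** Simulation with 172 analysed, balanced within strata, a true effect of 0.5 within-stratum SD and 20,000 runs per case:

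| Smaller stratum share, stratum difference in the contrast (assumed) | R² | Power without stratum | Power with stratum |
|---|---|---|---|
| 30%, 0.3 SD | 0.0185 | 0.900 | 0.904 |
| 30%, 0.5 SD | 0.0499 | 0.895 | 0.905 |
| 50%, 0.8 SD (extreme) | 0.1379 | 0.875 | 0.904 |

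R² here is p(1 − p)δ² / [1 + p(1 − p)δ²], for stratum share p and stratum difference δ.

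Attrition does not remove this loss. With δ/SE = 0.5/√(2/86) = 3.279 and R² = 0.05, power without the stratum is about Φ((3.279 − 1.96)/√0.975) = 0.909. With it, power is about Φ(3.279/√0.95 − 1.96) = 0.920. That is still about 1 point.

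**The case against.** The strongest reply is that the text nowhere says the listed effects are the only ones. This is a condensed article, and an analysis plan that is not shown may add the stratum. That stands as a limit: a reader might infer that the trial will certainly ignore its stratum, and the article does not establish this. It does not dispose of the point, because the article is not silent on the model. It names the fixed effects, and a plan that added the stratum would differ from the published list.

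The second reply is that the effect is small and on the safe side. This stands in full. The error rate is below nominal, the sample size does not move, and the assumed R² could be close to zero if nationality differences are stable over time. The article also gives no block or balancing details, so exact balance within strata is itself an upper-bound assumption.

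A reader might go further and infer that nationality drives the expected dropout, so that omitting it biases the result. The documents do not support that. The Sample Size section attributes the 50% to digital intervention studies generally, the feasibility trial and protocols of similar studies. No section links nationality to dropout. The mixed model also already conditions on the observed baseline and post-intervention scores. For bias, nationality would have to predict both dropout and unobserved 3-month change, differently by arm, given those scores. The article does not address this.

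**Conclusion.** The mismatch between the stratified randomization and the stated model is real, and its consequence is minor. For an assumed R² of 1-5% on the baseline-to-3-month contrast, standard errors are at most 0.5-2.6% too wide and type I error is 4.9-4.4%. With 50% random attrition these become roughly 0.25-1.3% and 4.9-4.7%. The power loss is about 0-1 point. A loss near 3 points needs an even split between strata and a 0.8 SD difference in change, which nothing in the article suggests.

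The planned 172 evaluable and 344 randomized are unaffected. No bias in the treatment contrast is shown. The case for changing the plan is that the analysis should follow the groups by which the trial randomizes, and that doing so costs almost nothing.

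**What to change.** Add the nationality stratum (Jordanian or Palestinian versus Syrian or other), as recorded at randomization, and the stratum-by-time interaction as fixed effects in the primary and secondary mixed models. The interaction matters most here, because a stratum main effect alone does little for a contrast taken relative to baseline. If the omission is deliberate, state why.

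The cost is a sentence of analysis wording and two fixed-effect terms in each model. The variable is already captured for allocation, and no change in sample size follows. The Results section reports that no data analysis had been conducted at the time of writing, so the terms could be prespecified without reference to outcomes. The article already provides for amendments and documented administrative changes.
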